### Study settings

As the quality of medical care in China is unbalanced distributed, we will carry out the study in hospitals respectively representing low (county hospitals), medium (small tertiary hospitals) and high levels (big tertiary hospitals with ACs) of anticoagulation management in Hunan province to comprehensively evaluate the SMART model. Three hospitals of each level are randomly selected, thus finally nine hospitals are included in this study. Our hypothesis is that the SMART model is not only better than the usual care (UC, physician managed clinics) and the AC management, but also could be applied in different levels of hospitals in China.

### Procedures

#### Training health care providers

All the participated health-care providers from nine hospitals will be organized together to receive both face-to-face seminar training courses and online meetings to master the study protocol and the measurements of managing patients. Table 1 shows the detailed training courses. In each hospital, a multidisciplinary team consisting of a physician and a pharmacist will manage their patients in the SMART model group together. For the three county hospitals, experienced pharmacists who manage the anticoagulation clinics in the tertiary hospitals will also join their multidisciplinary team to help manage patients with the aim of assuring patients’ safety.

**Table 1 Tab1:** Training courses for health care providers from participated hospitals

Training courses	Details
**Warfarin management**	1.Theoretical knowledge ① Basic knowledge of warfarin ② The standard protocol of warfarin management with patient self-testing ③ Warfarin monitoring and dosing at different situations ④ Adverse events treatment, including thrombosis, minor bleeding and major bleeding ⑤ Introduction of new oral anticoagulants ⑥ Laboratory tests interpretation ⑦ Patient education on warfarin, including medication adherence, drug/food interactions, diet, exercise and mental health 2. Practice in simulate patients 3. Tests to assess participant’s theoretical knowledge and practice skills
**Related-disease management**	1.Theoretical knowledge ① Atrial fibrillation ② Valvular heart disease ③ Deep venous thrombosis and pulmonary embolism ④ Stroke ⑤ coronary heart disease 2. Practice in simulate patients 3. Tests to assess participant’s theoretical knowledge and practice skills
**SMART Model**	1.Theoretical knowledge ① Usage of the POCT device ② Usage of the “XY” app ③ Stratified management based on patient risks ④ Communication skills with patients via the “XY” app ⑤ Communication between local hospitals and tertiary hospitals ⑥ Patients’ referral 2.Practice in simulate patients 3. Tests to assess participant’s theoretical knowledge and practice skills

#### Enrolling patients

Patients on warfarin attending the participated hospitals will be invited to join in the study. If the patients show interest, then the design and rationale of the study will be explained. The research staff will identify which patients are potentially suitable candidates for the study. After the eligible patients agree and sign the informed consents, the patients will be randomly assigned to either the SMART model group or the control group according to the protocol.

#### Baseline interview

All the participated patients will be required to complete a survey either via an online survey through their mobile phone or via a printed brochure. The contents of the survey contain three parts, including patients’ clinical parameters (warfarin indication, start date of warfarin, warfarin dosage, previous TTR, history of thrombosis or major bleeding, concomitant diseases and medicine), behaviour indicators (warfarin knowledge, anticoagulant compliance, treatment behavior and quality of life) and costs on warfarin related treatment.

#### Randomization

In low and medium level hospitals, only the UC group is used as the control group, thus eligible patients on warfarin will be randomly assigned to either the SMART model group or the UC group. While in the high level hospitals, both AC and UC are used as the control groups, thus eligible patients will be randomly allocated to the SMART model group, the AC group or the UC group. For each level of the three hospitals, a total of 120 patients in each arm will be enrolled. The flow chart of patients’ grouping and allocation is shown in Fig. 2. Patients’ randomization will be carried out by research staff using a standard protocol available in the website (http://stattrek.com/statistics/random-number-generator.aspx).

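### Recruiting-role staff allocate patients with a public random-number page; as stated, the method does not protect concealment, and no blocking or hospital stratification supports 120 per arm per level

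*Protocol article*

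**What the plan says.** Under Randomization, the article names both the operator and the tool: "randomization will be carried out by research staff using a standard protocol available in the website", followed by the address "http://stattrek.com/statistics/random-number-generator.aspx". Under Enrolling patients, "The research staff will identify which patients are potentially suitable candidates for the study", and assignment comes after eligibility and consent: "After the eligible patients agree and sign the informed consents, the patients will be randomly assigned".

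The Randomization section also fixes the numbers: "For each level of the three hospitals, a total of 120 patients in each arm will be enrolled". There are two arms in the lower two levels ("In low and medium level hospitals, only the UC group is used as the control group") and three arms (SMART, AC, UC) in the large tertiary hospitals.

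The article does not say whether numbers are drawn patient by patient or used once to build a list. It names no list holder, sealed or central release, blocking, or stratification by hospital within level.

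**The concern.** Naming a tool and an operator is more than silence about randomisation detail. A general number page, as described, has no link to a patient identifier, no lock after a draw and no study audit trail. Used patient by patient, it allows an unwelcome result to be drawn again. Used to make a list, it produces something that whoever holds it can read ahead. Either way, protection depends on someone independent of recruitment controlling the process, and the only role named is the one that also finds candidates.

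Two features of this trial make that matter. First, the care models cannot be masked from staff or patients. Second, SMART works only for patients who can handle the meter and the app, which staff can partly judge at screening. Under Educating and training patients, those allocated to SMART are excluded if their meter and laboratory INR differ by more than 0.3 units, or if they cannot report through the app. Staff therefore have a practical reason to prefer capable patients for SMART. If such patients also control their INR better, the TTR comparison is biased in favour of SMART, and adjustment for measured baseline factors cannot be relied on to remove it.

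A lesser concern is that a fixed 120 per arm per level, spread over three hospitals, needs some form of restriction, and none is described.

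**Working it through.** **1. The plan's own totals.** From 120 per arm per level: SMART 3 × 120 = 360, UC 3 × 120 = 360, AC 1 × 120 = 120, in all 840. These match the Abstract.

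**2. Who does what, side by side.**
- Enrolling patients: research staff identify candidates; assignment follows signed consent.
- Randomization: research staff allocate, using the public page.
- Educating and training patients: research staff supervise the SMART patients' meter check, after allocation.
- Follow-up visits and data collection: research staff collect the follow-up data.

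No separate allocator appears. The shared role name does not prove that the same individuals do all of this, but nothing stated separates them.

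**3. If each patient is drawn independently (an assumption), with totals fixed at 240 or 360 per level.**
- Two-arm level: P(exactly 120:120) = C(240,120)/2^240 = 0.051. P(an arm misses 120 by 10 or more) = 2 × P(X ≥ 130), X ~ Bin(240, 0.5), = 0.22. The 95% range for one arm is 105 to 135.
- Three-arm level: P(exactly 120 each) = 360!/(120!³ × 3^360) = 0.0023. The 95% range for one arm is 103 to 138.
- All three levels exact: 0.0514² × 0.0023 = 6.1 × 10⁻⁶.

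**4. If draws are independent but an arm closes when it reaches 120.** The target is met exactly, and the end of the sequence is determined. The expected forced tail in a two-arm level is 240 × C(240,120)/2^240 = 240 × 0.0514 = 12.3 allocations. In the three-arm level simulation gives about 10. These are foreseeable only to someone who knows the running count across the three hospitals of the level.

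**5. If a fixed-count list is made per level.** Each arm gets exactly 120, so the target is met. Balance within a hospital is not assured. For a two-arm hospital of 240/3 = 80 patients (equal recruitment assumed; not stated), the 95% range per arm is 33 to 47 (hypergeometric), against 31 to 49 with independent draws.

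**6. What imbalance costs.** Relative efficiency of a split a:b is 4ab/(a+b)². For 105:135 it is 4 × 105 × 135/240² = 56,700/57,600 = 0.984. The loss is under 2%.

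**7. With blocks within hospital.** Under equal recruitment there are 40 per arm per hospital, so 3 × 40 = 120 per arm per level. With unequal recruitment, each hospital stays balanced to within about half a block.

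Steps 3 to 5 cover the plausible readings. None of them supplies concealment, and none balances hospitals.

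**The case against.** The strongest reply is that this is an article. List holder, envelopes, blocks and strata are commonly left to the full protocol; a protocol version is named under Data monitoring but not shown, and the allocation flow chart (Fig. 2) is also missing from the text available. The article also does two things right: it places assignment after eligibility and signed consent, and it organises allocation by hospital level, which is the main gradient in care quality.

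Several stronger readings are tempting, and the documents do not support them:
- That numbers are drawn on demand for each patient. The text does not say so; the same page could generate a list in advance.
- That the plan cannot deliver 120 per arm. A fixed-count list, or filling each arm, gives exactly 120. The probabilities in step 3 hold only for independent draws with a fixed total and no cap.
- That the individuals who screen also randomise. This is inferred from a shared role name across nine hospitals.
- That chance imbalance between hospitals confounds the treatment effect. It adds variance, not systematic error, and the loss of precision is small.

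All four corrections stand. What remains is that the article did not leave the method open. It states a tool and an operator that do not in themselves provide concealment. Assignment after consent does not prevent a redraw or foreknowledge. If the full protocol contains safeguards, the published description should be corrected; if it does not, the method should be changed.

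**Conclusion.** The point holds as a weakness of the stated method. Allocation by the recruiting role with a public number page leaves concealment unprotected, and no blocking or hospital stratification stands behind the fixed 120 per arm per level. It is not evidence that allocation has been subverted, nor that the target numbers will be missed.

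The consequence that matters is possible selection bias in TTR. The documents give no basis for putting a size on it. The consequence that can be sized, chance imbalance, is minor: under 2% of efficiency at the edge of the 95% range in a two-arm level, and a matter of precision rather than validity. The conclusion assumes that the article describes the procedure actually followed. The hospital-level figures also assume equal recruitment of 80 patients per two-arm hospital.

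**What to change.** For the remaining recruitment (the article reports that it began in March 2021):
- Generate one permuted-block list in advance, stratified by hospital: 1:1 in county and small tertiary hospitals, 1:1:1 in large tertiary hospitals.
- Have it held by coordinating-centre staff who do not recruit, and release one allocation at a time after consent and eligibility are logged. Sealed numbered envelopes or the study database would both serve.
- Document how patients have been allocated so far: by list or by individual draw, by whom, and with what record.
- Include hospital, or at least hospital level, in the primary TTR model. Data analyses describes the group comparison as an unadjusted t-test or Mann–Whitney test and names no hospital term for its mixed model.

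The cost is a short amendment, a list made once and a little administration per allocation; no extra patients or assessors are needed. Patients already allocated cannot be protected retrospectively, which is why the record of past practice matters.

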**Fig. 2 Fig2:**
[figure not shown]
Flow chart of patients’ grouping and allocation in different levels of hospitals. AC: anticoagulation clinic; UC: usual care clinic; SMART: the “Safe Multidisciplinary App-assisted Remote patient-self-Testing” model

#### Educating and training patients

All the enrolled patients will attend a warfarin education session by the research team after they sign the informed contents. The educational courses will include the mechanism of action of warfarin, blood tests of INR and target ranges, follow-up frequencies, potential signs and symptoms of over-coagulation and under-anticoagulation, drug/food interactions with warfarin, lifestyle, missed doses, over doses, adverse events treatment, etc. All the above-mentioned knowledge will be printed out and given to patients for home study. For patients allocated to the SMART model group, they will further attend a training program in groups of less than three people. They will learn how to use the POCT device, as well as report their INR results and receive instruction of warfarin dosage and follow-up dates through the XY app. Later, patients are required to use the POCT device to perform at least two reproducible INR measurements under the research staff’s supervision. These results will be compared with the laboratory INR measurement from a venous blood sample. If there are wide differences (> 0.3 INR units) between the POCT and laboratory INR tests, patients will be excluded from the study [13]. Patients or their guardians who fail to use the XY app to report data will also be excluded from the study.

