### Outcomes

#### Primary outcome measure

The difference in TTR between the SMART model group and the control group during the 12 month period of study.

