#### Data analyses

We will report continuous variables as means ± SD and categorical variables as proportions. Data will be checked for normal distribution by means of the Kolmogorov–Smirnov’s test. In compliance with the distribution of data, Student’s t-test or Mann–Whitney’s U-test will be used for comparisons between the SMART model group and control group. Chi-square or Fisher’s exact tests will be used to compare between the SMART model group and control group with respect to categorical data. The control of anticoagulation will be assessed by evaluating TTR with the Rosendaal method [18] in each arm. The follow-up assessment data will be analyzed using Generalized Linear Mixed Model and survival analysis. *P* ≤ 0.05 is considered statistically significant. All tests are two tailed. From the perspective of health-care payer, we will conduct a cost-effectiveness analysis to assess the economic impact of the SMART model for warfarin home management. A Markov model, a half-cycle correction and a discount of 5% will be constructed or used to estimate the total costs and quality-adjusted life-years (QALYs) over the 2-year period (the outcomes beyond the observation period will be predicted according to the results obtained in the study). We will collect the direct and indirect costs of each enrolled patient on warfarin, evaluate their quality of life through EQ-5D-3L utility value from data provided by patients, calculate QALYs, and analyze the effects of multiple variables by the Linear Mixed Effects Model. The direct costs include laboratory INR test fees in the control groups (or POCT fees in the SMART model group), outpatient clinic visit fees (or supervision fees in the SMART model group), hospitalization fees and emergency room visit fees. The indirect costs include deducted income due to absence of working, traffic fees and accommodation fees. Because warfarin is very cheap, the medication fee of warfarin is not calculated in each group. The incremental cost effectiveness ratio (ICER) will be calculated according to the total costs and QALYs, and one-way and probabilistic analyses will be performed to verify the stability of the model.

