### Sample size determination

In order to detect a hypothetical TTR difference of 5% between the SMART model group and the control group with a power of 80% and a significance of *P* = 0.05, a sample size of 31 patients in each group is required [19]. An additional 10% is added to allow for patients dropping out of the study, thus a sample size of at least 34 patients in each arm is needed.

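### TTR comes from home meters in the SMART arm and apparently from laboratory INRs in the control arms, and the training screen does not bound the mean meter-laboratory bias

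*Protocol article*

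**What the plan says.** The primary outcome (Primary outcome measure) is "The difference in TTR between the SMART model group and the control group during the 12 month period of study". Under Data analyses, TTR is obtained in each arm by the Rosendaal method, which interpolates between successive INRs.

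The INRs behind it differ by arm. Under Intervention protocol, SMART patients test at home with a POCT device every two to four weeks. The section on control patients leaves their warfarin management as it is. No outcome definition names the control instrument, but the cost description under Data analyses lists "laboratory INR test fees in the control groups (or POCT fees in the SMART model group" among the direct costs, which points to the laboratory.

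One link between the two instruments is described. At training (Educating and training patients), SMART patients make at least two reproducible supervised meter readings, which are compared with a venous laboratory INR. Patients are excluded "If there are wide differences (> 0.3 INR units) between the POCT and laboratory INR tests". Controls have no such comparison, and no later paired test is described.

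The trial is sized (Sample size determination) "In order to detect a hypothetical TTR difference of 5% between the SMART model group and the control group".

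**The concern.** Randomization balances patients, not measuring instruments. If the meters on average read higher or lower than the laboratory, SMART TTR carries that error and control TTR does not. The observed difference then mixes the care model with the meter. Rosendaal TTR depends on whether INR lies either side of fixed limits, so a small offset matters when many readings lie near a limit.

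The 0.3 INR screen looks like protection, but it limits how far any one patient may be off. It does not limit the average across patients, and the average is what biases a comparison of means. What is at stake is whether a TTR difference near the planned 5 points can be attributed to the SMART model.

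**Working it through.** **1. The plan's own figure.** The protocol states 5 points, 80% power, alpha 0.05 ("All tests are two tailed") and concludes that "a sample size of 31 patients in each group is required". It gives no SD. With n = 2(1.96 + 0.84)² SD²/5², an SD of 7 gives 2 × 7.85 × 49/25 = 30.8, i.e. 31. The figure therefore implies an SD of about 7. That is a separate matter; here only the 5-point yardstick is used.

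**2. What the screen lets through.** Treat the meter-laboratory difference as normal with mean m and SD s. The share passing is Φ((0.3 − m)/s) − Φ((−0.3 − m)/s). Both m and s are assumptions.
- m = 0.1, s = 0.1: Φ(2) − Φ(−4) = 97.7% pass; mean among those retained 0.094.
- m = 0.15, s = 0.1: Φ(1.5) − Φ(−4.5) = 93.3% pass; retained mean 0.136.
- m = 0.2, s = 0.1: Φ(1) − Φ(−5) = 84.1% pass; retained mean 0.171.
- m = 0.2, s = 0.3: Φ(0.33) − Φ(−1.67) = 58.3% pass, so about 42% fail.

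The retained means treat the scatter as lasting differences between patients. If it is test-to-test noise, the screen does not reduce the mean bias at all.

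**3. Effect on TTR if dosing does not respond to the meter.** Assumptions not in the documents: target 2.0-3.0, lognormal INR, and the same true INR in both arms. A simple time-in-range example with median 2.0 and log-SD 0.25:
- True share in range = Φ(ln 1.5/0.25) − Φ(0) = Φ(1.622) − 0.5 = 44.8%.
- A meter reading 0.1 high shows in range when true INR is 1.9-2.9: Φ(ln 1.45/0.25) − Φ(ln 0.95/0.25) = Φ(1.486) − Φ(−0.205) = 51.3%.
- Shift: +6.5 points.

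Simulated Rosendaal TTR (tests every 21 days, between-patient log-SD 0.18, within-patient log-SD 0.22, correlation time 25 days) gives these shifts in points:

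| Median INR | −0.1 | +0.1 | +0.2 |
|---|---|---|---|
| 2.0 | −5.8 | +5.8 | +11.3 |
| 2.2 | −4.7 | +4.1 | +7.3 |
| 2.4 | −2.8 | +1.8 | +2.4 |
| 2.6 | −0.7 | −0.4 | −1.9 |

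**4. Effect if dosing follows the meter.** In the SMART arm it does, so step 3 is not the realistic case there. As a calculating device only, and not a proposed rule, let each patient's INR level move halfway (on the log scale) towards 2.5 whenever the meter reads outside 2.0-3.0. Other inputs are as in step 3, with starting medians 1.9-2.6:

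| Offset | Change in reported TTR | Reported minus laboratory-scale TTR, same patients |
|---|---|---|
| +0.1 | +1.5 to +2.1 | +2.1 to +3.9 |
| +0.2 | +2.9 to +4.2 | +6.0 to +9.9 |
| −0.1 | −2.0 to −1.5 | −1.3 to +0.1 |
| −0.2 | −3.9 to −3.1 | −0.5 to +2.0 |

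The last column is the measurement error that enters a comparison with laboratory-based controls. Feedback keeps the meter value in range while the true value drifts, so a high-reading meter flatters the arm. A low-reading meter produces little discrepancy.

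**5. Would an artefact of this size be noticed?** With 360 SMART and 360 usual-care patients, SE = SD × √(2/360). At an assumed SD of 20, SE = 1.49. A spurious 5 points would be significant with probability Φ(5/1.49 − 1.96) = 92%, and a spurious 3 points with probability Φ(3/1.49 − 1.96), about 52%.

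**The case against.** **This belongs in a statistical analysis plan.** That plan is not shown, and a journal article condenses. So the lack of a stated correction is not itself a fault, and it should not be inferred that none will be made. What stands is what the article does fix: an instrument that differs by arm, and a screen on individual differences only. Keeping the paired values, including those of excluded patients, is also a data-collection decision that cannot be left until analysis.

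**The meter is part of the intervention.** True, and dosing on it belongs to the effect under study. But TTR is meant to describe anticoagulation. If the meter misreads, patients steered off the laboratory range would still be scored as well controlled.

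**No bias has been shown.** Also true. Meter bias, target range, INR distribution and dosing response are all assumptions above.

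Three stronger readings are tempting and should be resisted.
- A reader might infer that a tolerated offset could equally create or hide the 5-point effect. That rests on the no-feedback figures. Once dosing follows the meter, the concern is mainly overstatement by a high-reading meter.
- A reader might infer from the cited TTR below 40% in China that this trial sits where the shift is largest. That figure describes care before the trial, not an actively managed SMART arm.
- A reader might infer that the screen would pass everyone with a uniform 0.2 offset. That needs almost no scatter: at scatter 0.1 about 16% would fail, and at 0.3 about 42%.

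**Conclusion.** The concern holds in a limited form. Instrument is confounded with arm in the primary comparison, and the training screen does not bound the mean bias. The laboratory source for controls is inferred from the costing text and the unchanged control management, not from an outcome definition.

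Size and direction cannot be known from the documents. On the assumed meter-guided model, which is nearer to how SMART works, an offset of +0.1 to +0.2 INR overstates laboratory-scale TTR by roughly 2 to 10 points against a planned effect of 5. The larger no-feedback shifts near a median of 2.0 are an upper illustration, and they vanish near 2.6. The documents do not support saying that the TTR result will be wrong, only that the design as described cannot tell a modest meter bias from a modest benefit. This is worth fixing, because the paired readings are already required.

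**What to change.** Keep the primary analysis as planned, and add the following before outcome data are examined.
1. Record and retain every meter-laboratory pair from training, including pairs from patients then excluded, so that the bias estimate is not truncated by the screen.
2. Estimate the mean meter-laboratory difference. Let it depend on INR only if the data support that, and allow for error in both methods.
3. Pre-specify a supportive sensitivity analysis that converts SMART meter INRs to laboratory-equivalent values, recomputes SMART TTR and carries the uncertainty of the correction through to the between-group difference.
4. Report it beside the primary result, not as a second condition for claiming superiority.
5. State the INR source for controls in the outcome definition.

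Precision should be adequate for the mean: with about 360 pairs and an assumed SD of 0.3, the standard error is 0.3/√360 = 0.016 INR. It will be poorer for an INR-dependent correction.

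The cost is a little analysis work, plus data capture if the paired values are not already being stored. The limitation is that training pairs do not capture later meter drift, and the report should say so.

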### Study participants and inclusion criteria

Patients eligible for this project have to comply with all of the requirements below: are expected to be on warfarin treatment for the duration of at least 12 months, accept the study protocol and randomization, and sign an informed consent. Patients who fall into any of the following criteria are excluded in this project, including pregnancy or plan to get pregnant in 18 months, had experienced a bleeding complication requiring treatment in the past 6 months, are unable to attend a hospital in 6 hours, renal failure (hemodialysis or glomerular filtration rate < 10 mL/min), dementia or unstable psychiatric conditions or receiving treatment for cancer.

A patient who has been enrolled in the project will be considered as a dropout if meets any of the following criteria and the reason will be recorded: the patient decides to withdraw for any reason; the patient in the SMART model group does not follow the health-care professionals’ instruction for at least twice; the researcher considers the patient is no longer physically and/or psychologically fit to remain in the study. The impact of dropouts on statistical analyses, including intention to treat, will be used by carrying the last observation forward.

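### Patients already randomised to SMART leave the study if they fail the POCT or app check, while controls face no such check, so the randomised comparison is not protected

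*Protocol article*

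**What the plan says.** The order of events is set out in two sections under Procedures. Enrolling patients: "After the eligible patients agree and sign the informed consents, the patients will be randomly assigned to either the SMART model group", with control as the alternative. Educating and training patients: everyone attends a warfarin education session, and then "For patients allocated to the SMART model group, they will further attend a training program in groups of less than three people". In that training, SMART patients make supervised POCT measurements that are compared with a venous laboratory INR. Where the difference exceeds 0.3 units "between the POCT and laboratory INR tests, patients will be excluded from the study". The section ends: "Patients or their guardians who fail to use the XY app to report data will also be excluded from the study".

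Control patients: controls receive the same education, and how their warfarin is managed is left alone. No device check, app check or adherence rule is stated for them. The eligibility criteria in Study participants and inclusion criteria do not require any ability to use the device or the app.

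That section also lists three dropout criteria. Withdrawal and the researcher's judgement of fitness apply to all arms. The third is written for one arm: "the patient in the SMART model group does not follow the health-care" professionals' instruction on at least two occasions. The article then mentions intention to treat and says that dropouts are handled by last observation carried forward.

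The Discussion names the exclusion of people who cannot use the device or the app as the study's biggest limitation. It does not mention that the exclusion acts on one arm after allocation.

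**The concern.** Randomisation makes the arms comparable only if everyone randomised is kept in the comparison. Here the SMART arm is filtered after allocation by device agreement and ability to report, and the control arm keeps people with the same difficulties. If those people tend to have poorer anticoagulation control, the remaining SMART patients would show a higher mean TTR than controls even if SMART did nothing.

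TTR over 12 months is the primary outcome, and the same patients are lost to the event, quality-of-life and cost comparisons. A later analysis plan could not repair this, because the rule takes patients out of the study and their follow-up data may never exist. Recruitment began in March 2021, so some may already have been lost.

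The rule on not following instructions twice raises a related but different problem: it may end observation early, in SMART only.

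**Working it through.** **1. Which patients are lost, and when**

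| Step | SMART | Controls |
|---|---|---|
| Consent, then randomisation | yes | yes |
| Warfarin education | yes | yes |
| POCT v laboratory INR check, out if > 0.3 | yes | none stated |
| App reporting check, out if failed | yes | none stated |
| Dropout after not following instructions twice | yes | none stated |
| Withdrawal; researcher's judgement | yes | yes |

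The two checks come after allocation and apply to one arm. Failing them is not among the three listed dropout criteria, so the sentence on last observation carried forward does not plainly cover these patients. If it were stretched to do so, a patient who left at training would have only the baseline TTR (from the preceding 12 months, Table 3) to carry forward.

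**2. The plan's own figures**

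Sample size determination gives a difference of 5 TTR points, 80% power, significance 0.05 and 31 per group. No SD is stated. From n = 2(1.96 + 0.8416)² SD²/5², n = 31 implies SD = 5 × √(31/2)/2.8016 ≈ 7.03. With SD = 7, n = 2 × 7.849 × 49/25 = 30.8, which rounds up to 31. Adding 10%: 31 × 1.1 = 34.1, in line with the stated 34. These steps supply the 5-point yardstick and the implied SD used below.

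**3. Size of the bias**

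Let f be the share of SMART patients excluded and d the amount by which their mean TTR is below that of the retained patients. The full-arm mean is (1 − f) × retained mean + f × excluded mean, so the retained mean exceeds it by f × d. The article gives neither f nor d; both are assumptions.

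| f | excluded of 360 | d = 5 | d = 10 | d = 15 |
|---|---|---|---|---|
| 10% | 36 | 0.5 | 1.0 | 1.5 |
| 20% | 72 | 1.0 | 2.0 | 3.0 |
| 25% | 90 | 1.25 | 2.5 | 3.75 |

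The range is 0.5/5 = 10% to 3.75/5 = 75% of the design difference.

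**4. Effect on the test if SMART has no effect**

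SE = SD × √(1/[n(1 − f)] + 1/n), and the false-positive rate is P(|Z + f·d/SE| > 1.96). Example with n = 360 per arm, f = 10%, d = 10 and an assumed SD of 20: SE = 20 × √(1/324 + 1/360) = 1.53; 1.0/1.53 = 0.65; the rate is 10%.

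| f, d | 360 v 360, SD 20 | 360 v 360, SD 7.03 | 120 v 120, SD 20 | 120 v 120, SD 7.03 |
|---|---|---|---|---|
| 10%, 5 | 6.2% | 15.3% | 5.4% | 8.4% |
| 10%, 10 | 10.0% | 45.9% | 6.6% | 18.9% |
| 20%, 10 | 24.4% | 94.9% | 11.3% | 54.7% |

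The nominal rate is 5%. For a given f and d, enrolling more patients leaves the bias unchanged and makes it more likely to reach significance. With all randomised patients followed and analysed as allocated, the term f × d is zero.

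**5. The rule on not following instructions twice**

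These patients are called dropouts and may stay in the analysis, so f × d does not apply to them. Under last observation carried forward their outcome stops at the second lapse, and whatever follows goes unrecorded. A control with the same lapses is observed to month 12. That is a conflict with intention to treat, of a size that the article does not allow one to estimate.

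**The case against.** The strongest reply has four parts.

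- **Dropouts are provided for.** The article mentions intention to treat with last observation carried forward. This stands for the rule on instructions: a reader might infer that such patients are removed from the analysis, but the text does not say so. It does not help patients who fail the POCT or app check, who are stated to leave the study and for whom no retention is described.
- **The direction is not shown.** The 0.3-unit criterion tests agreement between two INR measurements and does not measure adherence. A guardian may do the app reporting, so the filter is not simply one of ability. No TTR is given for patients who fail. This stands in part: the bias probably favours SMART for TTR, but a reader who takes the direction as proven, or as certain for costs and quality of life, goes beyond the text. The loss of comparability does not depend on direction.
- **The size rests on assumptions.** It does, and at the low end it is only half a TTR point.
- **The frequency of the instruction rule is unknown.** A reader might treat 13 to 26 scheduled tests a year as independent chances to lapse and conclude that most SMART patients could be lost. The article gives no lapse rate and does not say that a scheduled test counts as an instruction, and lapses within a patient are unlikely to be independent. No such figure is supportable.

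The acknowledgement in the Discussion does not answer the point, because a limit on whom the results apply to is different from a filter on one randomised arm.

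**Conclusion.** The concern holds and needs correcting. As written, patients randomised to SMART leave the study for failing a check that controls never take, and nothing in the text says that they are followed or analysed. For TTR the bias is f × d, probably toward SMART. Under assumed values of 10–25% excluded and a deficit of 5–15 points, it is 0.5 to 3.75 points against the 5-point design difference. Both inputs are assumptions, and the direction is a plausible inference. For events, quality of life and costs the comparison is equally unprotected, but the article gives no basis for a size.

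The SMART-only rule on not following instructions twice is a separate and lesser matter: it conflicts with the stated intention to treat because it can cut observation short in one arm.

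**What to change.** - State that every randomised patient stays in follow-up to month 12 and is analysed in the allocated arm, whatever care the patient then receives. INR, events, EQ-5D-3L and costs continue to be collected.
- Record failure of the POCT or app check as non-receipt of SMART, and not following instructions as non-adherence. Neither should end study participation.
- Reconcile the rule on not following instructions twice with intention to treat, so that it does not end data collection. Whether it ends remote management is a clinical matter on which this review takes no position; the article should say which is meant.
- Recover INR and event records, where possible, for patients already excluded since March 2021.
- Use the trained and adherent subset only for a supportive per-protocol analysis.
- If the check is instead moved before randomisation, do so for all candidates at all nine hospitals. Moving it at some sites only would give different entry populations by site in the middle of recruitment.

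The cost is amendment wording and the follow-up of patients who would otherwise have been dropped. The estimated effect may be smaller, because it will include patients who could not use SMART. A check before randomisation would add training time for patients who are then allocated to control.
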